#### Caregiver surveys:

- In-person: research assistant/coordinator may administer the patient survey in-person.
- Email: the surveys will be sent by email through REDCap
- Text message: the surveys will be sent by text message through REDCap (REDCap + Twilio module)
- Phone: research assistant/coordinator will administer the paper survey over the phone and input the data into REDCap
- Paper mail: the paper survey will be sent by mail through USPS to the subject. We will also include a pre-addressed/stamped envelope for participants to mail their completed survey back to the study team.

#### Clinician surveys

- E-mail: surveys will be emailed to clinician subjects through REDCap
- Text message: the surveys will be sent by text message through REDCap (REDCap + Twilio module)

#### 5.5.1 Primary endpoint

| Measure                                                                                   | Source                                                                                | Day(s) Obtained |
|-------------------------------------------------------------------------------------------|---------------------------------------------------------------------------------------|-----------------|
| Total cost, hospitalization (published as percent change given sensitivity of these data) | Intervention arm: Home hospital accounting
Control arm: hospital accounting system | Discharge       |

#### 5.5.2 Secondary endpoints

| Measure                                                                                                       | Source                     | Day(s) Obtained         |
|---------------------------------------------------------------------------------------------------------------|----------------------------|-------------------------|
| Total cost, discharge to 30-days post discharge (published as percent change given sensitivity of these data) | Hospital accounting system | 30 days after discharge |
| Unplanned readmission within 30-days of discharge, %                                                          | EHR and patient report     | 30 days after discharge |
| Days at home (the number of days spent at home from the day of discharge to 30-days later)                    | EHR and patient report     | 30 days after discharge |
| Percent of day lying down                                                                                     | Biometric monitor          | Each day of             |

|  |  |           |
|--|--|-----------|
|  |  | admission |
|--|--|-----------|

### 5.5.3 Exploratory endpoints

#### Health Care Utilization

| Measure                                                | Source                                                                            | Day(s) Obtained |
|--------------------------------------------------------|-----------------------------------------------------------------------------------|-----------------|
| Length of stay, days                                   | RA via MD/RN for home patients; RA EHR review for inpatients                      | Discharge       |
| IV medication, days                                    | As above.                                                                         | Daily           |
| Intravenous fluids, days                               | RA via EHR / administrative data                                                  | Daily           |
| Intravenous diuretics, days                            | RA via EHR/ administrative data                                                   | Daily           |
| Intravenous antibiotics, days                          | RA via EHR/ administrative data                                                   | Daily           |
| Oxygen requirement, days                               | RA via EHR / administrative data                                                  | Daily           |
| Nebulizer treatment, days                              | RA via EHR / administrative data                                                  | Daily           |
| Imaging, %                                             | RA via EHR / administrative data                                                  | Daily, +30      |
| Lab Orders, #                                          | As above.                                                                         | Daily, +30      |
| MD sessions, # of notes                                | As above.                                                                         | Daily, +30      |
| Consultant sessions, # of notes                        | As above.                                                                         | Daily, +30      |
| PT/OT sessions, # of notes                             | As above.                                                                         | Daily, +30      |
| Disposition (routine, SNF, home health, other)         | RA via MD/RN for home patients; RA EHR review for inpatients/ administrative data | Discharge       |
| Follow up with patient's PCP within 14 days, y/n       | RA via pt phone call, cross checked with EHR data                                 | +30             |
| SNF utilization, days                                  | As above.                                                                         | +30             |
| Home health utilization, days                          | As above.                                                                         | +30             |
| Unplanned readmission(s) after index, # and y/n + date | As above.                                                                         | +30             |
| ED observation stay(s), # and y/n + date               | As above.                                                                         | +30             |
| ED visit(s), # and y/n + date                          | As above.                                                                         | +30             |

RA: Research assistant

#### Safety

| Measure                                | Source                                                                                                                                                                          | Day(s) Obtained |
|----------------------------------------|---------------------------------------------------------------------------------------------------------------------------------------------------------------------------------|-----------------|
| Fall                                   | RA via MD/RN for home patients; MD EHR review for inpatients                                                                                                                    | Daily           |
| Delirium                               | RNs in home and inpatient settings calculate the CAM (standard of care in both). RA will obtain the home patient CAM via the home RN; RA will obtain the inpatient CAM via EHR. | Daily           |
| DVT/PE                                 | RA via MD/RN for home patients; MD EHR review for inpatients                                                                                                                    | Daily           |
| New pressure ulcer                     | As above.                                                                                                                                                                       | Daily           |
| Thrombophlebitis at peripheral IV site | As above.                                                                                                                                                                       | Daily           |
| Hospital Acquired Condition     |                                                                                                                                                                                 |                 |
| CAUTI                                  | As above.                                                                                                                                                                       | Daily           |
| Clostridium difficile                  | As above.                                                                                                                                                                       | Daily           |

|                                        |                                                              |           |
|----------------------------------------|--------------------------------------------------------------|-----------|
| MRSA                                   | As above.                                                    | Daily     |
| New arrhythmia                         | As above.                                                    | Daily     |
| Hypokalemia                            | As above.                                                    | Daily     |
| Acute kidney injury                    | As above.                                                    | Daily     |
| Medication error                       | As above.                                                    | Daily     |
| Unanticipated mortality                | As above.                                                    | Daily     |
| Loss of consciousness                  | As above.                                                    | Daily     |
| Transfer back to hospital a | RA via MD/RN                                                 | Discharge |
| Unplanned mortality during admission   | RA via MD/RN for home patients; MD EHR review for inpatients | Discharge |
| Unplanned 30-day mortality             | RA via pt/caregiver call                                     | +30       |

a: intervention arm only

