| Personnel     | [figure not shown] [figure not shown]
Nurse/Paramedic 
 
• 2 daily visits (1 in-person; 1 virtual)
 
• Medication administration
 
• IV access management
 
• Education
 

Physician 
 
• 1 daily interaction
 
• Medical decision making
 
 |
| Diagnostics   | Point of care: BMP, Hgb/Hct, PT/INR, ultrasound, x-ray, PFTs, ECG                                                                                                                                                                                                                                                                                                                                                                                                                                                      |
| Pharmacy      | Any inpatient medication, most any route                                                                                                                                                                                                                                                                                                                                                                                                                                                                               |
| Equipment     | Ambulatory infusion pump, peripheral IV, oxygen concentrator                                                                                                                                                                                                                                                                                                                                                                                                                                                           |
| Communication | Telepresence/virtual visits                                                                                                                                                                                                                                                                                                                                                                                                                                                                                            |

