**Table 1**

As denoted in the table above, the physician will make at least one daily virtual visit to the patient's home, facilitated by the nurse/paramedic. At the discretion of the physician and nurse/paramedic, the physician can make additional virtual visits should the patient's clinical condition require it. Similarly, the nurse/paramedic will make at least two daily visits to the patient's home. At the discretion of the physician and nurse/paramedic, the nurse/paramedic can make additional visits should the patient's clinical condition require it. This will be an ongoing twice daily discussion among clinicians, patient, and caregivers, as applicable. A patient or

549 clinician can initiate a video visit at any time. As denoted in the table above, the RHH team uses  
550 a suite of communication software to communicate with the patient and among team members.  
551 The nurse or paramedic will provide technology training to the patient (as needed) at admission  
552 and the rural home hospital team will be available to provide any technical assistance to subjects  
553 as needed.

554  
555 For patients with chronic/stable dementia, they will receive mental status assessments (eg,  
556 Confusion Assessment Method) by the home hospital RN/paramedic at each visit (at least 2  
557 daily). As is standard of care, we will take measures to avoid delirium: open blinds to allow light  
558 in during the day, minimize environmental noise, encourage typical routines to optimize eating  
559 and sleeping, and reassess medication list for culprit medications.

560  
561 Clinical parameters measured will be at the discretion of the physician and nurse/paramedic, who  
562 treat the participant following evidence-based practice guidelines, just as in the usual care  
563 setting. Monitoring will be performed by RHH clinicians. The clinical home hospital team  
564 manually checks vital signs at least daily. If deemed necessary based on a patient's acuity, the  
565 home hospital team can visit additional times. At all times, the patient and care team have 24/7  
566 access to the RHH attending physician.

567  
568 On top of this "on-the-ground" team, the home hospital attending is notified with an alarm  
569 should there be delayed data transfer. Such an alarm would cause the attending to contact the  
570 patient as deemed clinically appropriate.

571  
572 Please see below for all collected data points.

573  

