574 Documentation by RN/paramedic and MD will occur via digital intake notes, daily progress  
575 notes, and discharge notes that will be compiled (on a secure shared drive) and uploaded as a  
576 scanned document to the patient's chart upon discharge.

[figure not shown]

**Figure 1** RHH flow. Note a patient may **enter** this flow from their home, a clinic, the emergency department, or the hospital floor. The patient is triaged by the RHH nurse with as needed assistance of the RHH MD. The RHH nurse/paramedic deploys in the patient's home, facilitates a medical evaluation by a remote MD, welcomes and educates the patient, and sets up monitoring and communication technology. The nurse rounds at least once daily in person, facilitating an interaction with the RHH MD. Finally, the patient is discharged using the same criteria for discharge as would be used in a traditional hospital (ability to perform activities of daily living given supports in the home).

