## 8.0 POTENTIAL BENEFITS

### **Patients (home hospitalization group):**

- Remain in their home despite acute illness
  - Eat their own culturally concordant food
  - Sleep in familiar surroundings
  - Maximize time and interactions with their family and friends
- Improved health outcomes (we anticipate these from previous literature)
  - Reduced length of stay

- Reduced complications while admitted
  - Less delirium
  - Fewer falls
  - Fewer health care associated infections
  - Decreases reduction in functional status
- Improved patient experience
- Clinical improvements to the standard of care
  - Minimally invasive continuous vital signs, telemetry, and activity tracking;
  - On-demand 24/7 clinician virtual video visits;
  - Ambulatory/portable infusion pumps that can be worn on the hip;
- Improved transitions of care
  - Ability to coach patients on their post-discharge care plan in the appropriate environment, with caregivers available, and with adequate time for teaching given provider to patient ratio

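### Delirium is ascertained differently in the two arms: CAM frequency, mode, assessor and data source are not matched, so the comparison may be biased in either direction

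*Protocol*

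**What the plan says.** Delirium is an exploratory safety endpoint, obtained daily (section 5.5.3, Safety table). The table says "RNs in home and inpatient settings calculate the CAM (standard of care in both", and then sets two routes for the data: "RA will obtain the home patient CAM via the home RN; RA will obtain the inpatient CAM via EHR".

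Section 5.1 describes the home contacts. Table 1 lists "2 daily visits (1 in-person; 1 virtual" for the nurse or paramedic. The text below it makes two a minimum ("the nurse/paramedic will make at least two daily visits"), and the legend to Figure 1 adds "The nurse rounds at least once daily in person".

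The same section has one sentence on mental status: "For patients with chronic/stable dementia, they will receive mental status assessments", with the CAM as the named example, "by the home hospital RN/paramedic at each visit (at least 2" daily).

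Section 8.0 lists "Less delirium" among the benefits anticipated for the home group. No section states how many CAMs a day are done on the ward, whether a CAM may be done by video, or which CAM counts when a day holds several.

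**The concern.** Delirium fluctuates, so whether a patient is recorded as delirious depends on how often, how and by whom the patient is assessed. Section 3.2 excludes patients with acute delirium at entry, so every counted case is a new episode that must be detected during the stay.

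Here the arm sets the conditions of detection. Home patients are seen at a small number of scheduled contacts, some by video, and the result is obtained from the nurse. Ward patients are under inpatient nursing, and the result is whatever was charted. The raters know the arm. Delirium is also not among the events that section 9.0 sends to the blinded monitoring committee, so nothing later evens this out.

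At stake is the reading of any difference in delirium, an outcome on which the protocol expects a home benefit. Such a difference could reflect the measurement and not the care.

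**Working it through.** **1. The two passages side by side**

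| | Section 5.5.3, Safety table | Section 5.1, text after Table 1 |
|---|---|---|
| Who is assessed | patients in both settings, no restriction | home patients with chronic or stable dementia |
| By whom | RN | RN or paramedic |
| How often | obtained daily; number per day not stated | each visit, at least 2 a day |
| Instrument | CAM | mental status assessment, CAM as the example |
| Mode | not stated | each visit; one of the two scheduled contacts is virtual (Table 1) |
| Source | home: from the RN; ward: from the EHR | not stated |

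The passages can be read together, as a general rule plus an added rule for dementia patients. Even so, for a home patient without dementia the number of CAMs per day, and whether a paramedic may do them, is open. For ward patients the number is open throughout.

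**2. Can the direction of bias be determined?**

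The protocol gives no rate, effect or power for delirium, so there is no figure to reproduce. What follows is an illustration only.

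From the protocol: true delirium 20% in both arms (the background figure in section 1.1), and two home contacts a day, one in person and one virtual.

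Assumed, not in the protocol: a CAM is done at both home contacts; one CAM detects delirium on a delirious day with probability s = 0.5; a virtual CAM is half as sensitive (0.25); the episode lasts one day; the ward does 1 to 6 CAMs a day; the chart captures either all of the ward's detection or half of it (s = 0.25 per look).

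Formula: recorded rate = 20% × [1 − product of (1 − sensitivity of each look)].

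Home: 20% × [1 − 0.5 × 0.75] = 20% × 0.625 = 12.5%.

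| Ward CAMs per day | Chart capture | Ward recorded rate | Home:ward ratio |
|---|---|---|---|
| 1 | full | 20% × 0.5 = 10.0% | 1.25 |
| 2 | full | 20% × (1 − 0.5²) = 15.0% | 0.83 |
| 3 | full | 20% × (1 − 0.5³) = 17.5% | 0.71 |
| 6 | full | 20% × (1 − 0.5⁶) = 19.7% | 0.63 |
| 2 | half | 20% × (1 − 0.75²) = 8.8% | 1.43 |
| 3 | half | 20% × (1 − 0.75³) = 11.6% | 1.08 |

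If the virtual look is as good as the in-person one and the ward does two fully charted CAMs, both arms record 15.0% and the ratio is 1.00.

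**3. Range**

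The inputs were varied over s = 0.3, 0.5 and 0.7; virtual sensitivity half or equal; an episode of one or two days; 1, 2, 3 or 6 ward CAMs a day; and chart capture half or full.

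- Lowest ratio, 0.46: s = 0.3, virtual half as sensitive, one day, six fully charted ward CAMs. (1 − 0.7 × 0.85)/(1 − 0.7⁶) = 0.405/0.882.
- Highest ratio, 3.40: s = 0.3, virtual equal, one day, one half-captured ward CAM. (1 − 0.7²)/0.15 = 0.51/0.15.

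Longer episodes shrink the effect. At s = 0.5 with the virtual look half as sensitive and two fully charted ward CAMs, a two-day episode gives 17.2% against 18.8%, a ratio of 0.92 instead of 0.83.

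True delirium is equal in the two arms throughout, so every departure from 1 comes from ascertainment. The sign depends on ward frequency and chart capture, neither of which is stated.

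**The case against.** The strongest defence is that the protocol names one instrument, calls it standard care in both settings and obtains it daily in both. Two home visits is a minimum, and a rule for several CAMs in one day may sit in an analysis plan that is not shown. Delirium is one of many exploratory measures, and section 8.0 presents its benefits as expected from earlier literature, not as a trial hypothesis. All of this is fair and keeps the point modest. It does not remove the different data routes, the virtual contact or the unmatched schedules. These concern collection, and an analysis rule can correct them only if comparable CAMs exist.

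A reader might go further in two ways that the documents do not support.

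- **That home assessment is limited to dementia patients.** Section 5.1 does not say so. It sets a per-visit rule for that group, and the Safety table covers home patients without restriction.
- **That home patients get fewer looks, so the bias favours home.** Ward nurses are present around the clock, but that is not a CAM frequency. Assuming three ward CAMs against two equally sensitive home CAMs, at s = 0.5 and a one-day episode, gives 15.0% against 17.5%, a spurious reduction of 1 − 15.0/17.5 = 14%. The arithmetic is right, but the three is assumed. With one ward CAM, or poor charting, the sign reverses. Asking the home nurse directly may also find more than a chart does.

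An objection to matching is that ward patients have no home visit whose hour could be matched, and that a daytime rule discards night-time delirium. A fixed common window answers the first part. The second is a real cost, handled under the fix.

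**Conclusion.** The concern holds as a weakness of measurement. CAM frequency, mode, assessor and data source are not standardised across arms, and sections 5.1 and 5.5.3 differ on who is assessed, by whom and how often. The delirium comparison may therefore be biased in either direction.

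The size cannot be derived from the protocol. The ratios of 0.46 to 3.40 show only that the sign is open. They rest on assumed per-look sensitivity, virtual sensitivity, ward frequency, chart capture and episode length, and on a 20% background rate that is not specific to this trial's population.

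Neither a bias towards home nor a restriction of home CAMs to dementia patients is established. Delirium is exploratory and has no power calculation, and the primary cost result is unaffected. This is a worthwhile, inexpensive improvement and not a threat to the trial's main conclusion.

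**What to change.** 1. Reconcile section 5.1 with the Safety table: state who is assessed with the CAM, by which staff and how often, in each arm, and whether a video assessment counts.
2. Define the compared outcome from one CAM per patient-day in both arms, within a prespecified common daytime window: the in-person CAM at home, and the charted CAM in the same window on the ward. If the window holds more than one, fix in advance which is used.
3. Take the result from the written record in both arms. At home, the nursing visit form that section 5.5 already requires after each visit could carry it.
4. Count a missing CAM as missing, not as negative.
5. Report delirium from all CAMs as a supporting analysis, and the number of CAMs completed per patient-day by arm.

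The cost is a wording change, an extraction rule and possibly one field on an existing form. The downside is that delirium seen only outside the window leaves the compared outcome, so there are fewer events; the supporting analysis keeps those events visible. The raters would still know the arm, which this change does not cure.

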## **3.0 SUBJECT SELECTION**

### 3.1 Inclusion

#### Patient inclusion criteria:

##### Patient clinical inclusion criteria:

- $\geq 18$  years old
- Any infectious process (e.g., pneumonia, diverticulitis, cellulitis, complicated urinary tract infection)
- Heart failure exacerbation
- Asthma and chronic obstructive pulmonary disease exacerbation
- Atrial fibrillation with rapid ventricular response
- Diabetes and its complications
- Venous thromboembolism
  - This includes a patient who requires therapeutic anticoagulation and concomitant monitoring (thus requiring inpatient status)
- Gout exacerbation
- Chronic kidney disease with volume overload
- Hypertensive urgency
- End of life / desires only medical management
  - This includes a patient who requires acute care for symptom management but declines any surgical intervention. This may include a patient who is about to transition to hospice care, for example, but still has the functional capacity to meet our criteria below. Under these circumstances, we would make sure that various contingencies, including possible transition to hospice care or hospital readmission, are completely understood by patients and caregivers as applicable.

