**Figure 2**

#### 4.3 Treatment Assignment

- If the participant consents, the research assistant will proceed to randomization via concealed envelopes with
  - Concealed allocation;
  - Stratified on diagnosis:
    - infection,
    - heart failure,
    - chronic obstructive pulmonary disease or asthma, and
    - other diagnosis;
  - Randomly selected block sizes between 4 and 6;
  - Use randomization to determine arm.
- If patient/caregiver does not consent, the research assistant will ask the patient's permission to collect covariates, functional status, and a quality-of-life measure to determine generalizability of enrollment.
- Participants randomized to the control group will receive usual care at the hospital, from an attending general internist.

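### All three mortality outcomes are limited to an undefined subset of deaths, and no all-cause mortality outcome is listed

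*Protocol*

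**What the plan says.** The Safety table in Protocol Section 5.5.3 has three rows on death: "Unanticipated mortality", collected daily; "Unplanned mortality during admission", collected at discharge; and "Unplanned 30-day mortality", collected 30 days after discharge. For the two in-admission rows the source is "RA via MD/RN for home patients; MD EHR review for inpatients" (the daily row refers back to the same entry higher in the table). For the 30-day row it is "RA via pt/caregiver call". The Protocol defines neither unplanned nor unanticipated, and none of its endpoint tables contains a row for death from any cause.

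Section 3.1 makes patients eligible under the heading "End of life / desires only medical management" and adds: "This may include a patient who is about to transition to hospice care, for example". Under Section 4.3 randomisation is "Stratified on diagnosis", with strata for infection, heart failure, obstructive airway disease and other. End of life is not a stratum.

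Section 9.0 (Safety monitoring) has a list of events that go to a blinded committee. Death during admission is on it without any qualifier; death after discharge is not. The committee's stated task is to decide whether the event is attributable to the intervention.

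**The concern.** Death is the safety outcome that needs least judgement. Restricting it to deaths that someone regards as unplanned brings judgement back in. In most trials of acute care few deaths would be in dispute. Here some patients are enrolled close to hospice, so for them the question of whether a death was planned is a real one.

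The place of care cannot be concealed from those giving it, and the information on an in-admission death comes from the treating team in one arm and from a physician's chart review in the other. If the two routes lead to different habits of labelling, the tabulated mortality can differ between arms when true mortality does not, or agree when it does not. The reader of the results would have no unrestricted count in the listed outcomes against which to check this.

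**Working it through.** The Protocol states no mortality rate, margin or power for death, so there is no figure to reproduce. The check has two parts.

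**1. What the Protocol captures, side by side**

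| Item | Which deaths | Home arm source | Hospital arm source |
|---|---|---|---|
| Safety table, daily row | Unanticipated, undefined | Treating physician or nurse, through the research assistant | Physician chart review |
| Safety table, discharge row | Unplanned, undefined | Same as above | Same as above |
| Safety table, 30-day row | Unplanned, undefined | Call to patient or caregiver | Call to patient or caregiver |
| Section 9.0 committee trigger | Any death during admission | Blinded review of attribution | Blinded review of attribution |

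Three things follow. First, no row gives an all-cause comparison between arms. Second, the unqualified trigger in Section 9.0 does not match the qualified in-admission rows in Section 5.5.3. Third, the daily and discharge rows share their sources and cover the same period, and nothing in the text tells them apart.

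**2. How much labelling could matter (illustration)**

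Inputs:
- *n* = 75 per arm, the recruitment hoped for in Section 6.1 (the power calculation uses 66).
- *d* = the all-cause death proportion. The Protocol gives none, so it is an assumption, shown over a range.
- *s* = the share of deaths labelled planned. This is also an assumption.

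Expected deaths per arm = *n* × *d*:
- 75 × 0.03 = 2.25 and 75 × 0.05 = 3.75, or about 2 to 4.
- With 66 per arm: 66 × 0.03 = 1.98 and 66 × 0.05 = 3.30.

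Effect of relabelling on one arm's count: 1 of 4 is 25%; 2 of 2 is 100%.

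Expected counted deaths = *n* × *d* × (1 − *s*). If true mortality is the same in both arms, the ratio of counted deaths, home to hospital, is (1 − *s*home) / (1 − *s*hospital), whatever *n* and *d* are:
- 50% labelled planned in both arms: 0.50 / 0.50 = 1.00.
- 70% at home, 30% in hospital: 0.30 / 0.70 = 0.43.
- 30% at home, 70% in hospital: 0.70 / 0.30 = 2.33.

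Counted deaths in the 70%/30% case, home against hospital, with 75 per arm:
- *d* = 3%: 0.68 against 1.57.
- *d* = 6%: 1.35 against 3.15.
- *d* = 10%: 2.25 against 5.25.

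Equal labelling does no harm to the ratio. Unequal labelling can move it well away from 1 in either direction. The shares of 70% and 30% are chosen to show the mechanism; nothing in the Protocol suggests these particular values.

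**The case against.** Several stronger conclusions are tempting, and the Protocol does not support them.

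- *Deaths labelled planned are lost.* Not so for deaths during admission. Section 9.0 sends all of them to a blinded committee, whatever the label. What stands is that this review concerns attribution, omits deaths after discharge and produces no outcome by arm.
- *Staff who know the arm apply the label after the event.* A reader might infer this from the data sources, but the table names where information comes from. It does not say who classifies a death, when, or with what knowledge of the arm. A definition may exist in the Monitoring Plan or in a statistical analysis plan, neither of which is shown. That could settle the meaning of unplanned. It would not by itself turn a restricted outcome, which the Protocol fixes, into an all-cause one.
- *The trial's claim of similar safety fails.* The Protocol makes no such claim for this trial. The statement in Section 1.1.1 describes earlier studies, and the aims in Section 2.0 concern cost, days at home, activity, readmission and lessons for dissemination.
- *One death counts twice.* No composite or summed count of deaths is planned. The two in-admission rows are redundant, which is untidy but not double counting.

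Two further points against the concern are fair. Separating expected from unexpected deaths is a reasonable aim when patients near hospice are enrolled. And with 2 to 4 deaths per arm, all-cause counts would not establish similar mortality either. Both are arguments about how to present and read the results. Neither is a reason to leave out the unrestricted count, and the first can be met by a split fixed before randomisation.

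**Conclusion.** The point holds as a defect in how exploratory safety outcomes are defined. Every mortality outcome is confined to an undefined subset of deaths, no all-cause outcome is listed, end-of-life patients are eligible, in-admission deaths are sourced differently by arm, and Sections 5.5.3 and 9.0 do not agree on which in-admission deaths are of interest. Differential labelling could mask or create a difference; the Protocol does not show that it will.

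The size rests on assumptions: 3% to 5% mortality and 75 patients per arm give about 2 to 4 deaths per arm, so one or two labels matter. The primary cost analysis is untouched. The change should be made, because it is cheap and removes an avoidable route to bias, but it does not call the trial's main result into question.

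**What to change.** In the Safety table of Section 5.5.3:

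1. Replace the three rows with two: all-cause death during the index admission, and all-cause death to 30 days after discharge. Report both by arm. This merges the two overlapping in-admission rows and brings the table into line with the unqualified wording in Section 9.0.
2. Keep unplanned death only as a supportive split. Define it by information recorded before randomisation, namely entry under the end-of-life criterion or admission code status, or have the blinded committee classify it. The covariate table times code status to admission without saying whether that precedes randomisation, so this must be fixed if code status is used. If the committee classifies, its remit must be extended to planned status and to deaths after discharge.

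The cost of the first item is essentially wording, since a death has to be identified before it can be labelled. Extending the committee's remit would add a little work, on few cases. The reported death rate may be slightly higher than under the restricted definition.
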